**Methods/Design:**

Phase 1: The systematic identification of determinants of the implementation of FTE among therapists and the elderly. A questionnaire study was conducted in a random sample of 100 therapists, and interviews took place with 23 therapists and 8 elderly people (aged 66 to 80 years). The determinants were broken down into four categories: the characteristics of the environment, the organisation, the therapists, and the training programme.

Phase 2: Developing and applying strategies adapted to the determinants identified. Fifteen physiotherapists will be trained to provide FTE and to recruit elderly people living at home. The therapists will then deliver the 12-week programme to two groups of elderly, each consisting of six to twelve people aged 70 years or older.

Phase 3: Study of implementation and the impact. To study the actual use of FTE: 1) therapists record information about the selection of participants and how they apply the key features of FTE, 2) the participating elderly will keep an exercise logbook, 3) telephone interviews will take place with the therapists and the elderly and there will be on-site visits. The effects on the elderly people will be studied using: 1) the Patient-Specific Questionnaire, the Timed Up and Go test and a two performance tests. All tests will be performed at the start of the FTE programme, half way through, and at the end of the programme.

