Increasing physical activity in the elderly is therefore a relevant and important issue and so we decided to study the implementation of an evidence-based programme for elderly people living at home: Functional Task Exercise (FTE). By contrast with most other exercise programmes for older people, FTE is based on state-of-the-art knowledge about human movement sciences, action theory, motor learning, motivation, rehabilitation medicine, development of frailty and cognitive psychology [10-12]. Previous research looking at older women has shown that, by comparison with the usual care, i.e. strength exercise, FTE is more effective in improving functional performance, and that FTE is the first exercise programme with sustainable effects [11,12]. It is assumed that FTE achieves enduring effects because it enhances older people’s physical capacity and also because it fits in with daily routines. This clearly differentiates FTE from other programmes in regular use. The single-blinded RCT conducted by De Vreede et al. [10,12,13] found an effect size of 1.25, with an average increase of 15%, on the Assessment of Daily Activity (ADAP) test. This is generally considered to be a large effect size [13] and thought to be relevant [11]. Moreover, the FTE programme was very much appreciated by the older participants: they rated it 8.6 on an 11-point scale [14]. Training compliance was also high: an average of 90% of the participants attended all the training sessions [14]. More details about FTE can be found in the methods section.

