#### Participants

Fifteen physiotherapists and/or remedial therapists will be recruited. Inclusion criteria are:

a) therapists have to be working with elderly people,

b) therapists are willing to implement FTE in their practices,

c) therapists are willing to follow the FTE training,

d) therapists are willing to participate in the study,

e) therapists have graduated and are formally registered with their professional organisations,

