#### Participants

Each physiotherapist or remedial therapist who completes the training course will deliver the FTE programme to two groups of elderly people. The second group will start when the first group has finished the 12-week FTE programme. To safeguard against possible therapist drop-out, one extra therapist will be trained. Each group consists of six to twelve elderly people aged 70 years or older who have slight problems with activities of daily living. The targeted elderly people will live independently and be willing to follow FTE to improve their independence and their activities of daily living. They will also have to be able to exercise strenuously without being limited by comorbidities or other disabilities.

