#### Method

##### Evaluation of process of implementation

The therapists will keep records about how they recruit elderly people and of the reasons for participation/non-participation of the elderly. Furthermore, during the 12-week FTE programme, the therapists will keep records of the number of participants who are present and the reasons for any absence.

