##### Effects of the adjusted FTE

Therapists will recruit the elderly and train them using the FTE programme. Before the start of the FTE programme, there will be an intake procedure to check for comorbidities and other limiting factors. During the intake and at the start of the FTE programme, the following questionnaire and tests will be used:

the Patient-Specific Questionnaire (PSQ – in Dutch, the “PatientSpecifiekeKlachtenlijst”) measures the functional status of a patient with respect to the three to five most important physical complaints [26];

the Timed Up and Go test (TUG) measures the basic mobility of older people [27];

the 10 meter walking test measures the walking speed;

a patient-specific performance test (related to the goals of the patient as determined by the PSQ). This test can be different for each participant since it is related to their specific, personal physical problem.

The PSQ questionnaire and the tests will be repeated halfway and at the end of the FTE programme in order to document changes and to provide the therapist with additional information about how to adjust training intensity.

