#### Analysis

Qualitative analyses will be used to evaluate the implementation strategy. ANOVA for repeated measures will be used to determine the effect of the FTE programme.

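### Repeated-measures ANOVA over three test moments by default uses only people with all three values, so the result would describe completers, while the aim is the effect in daily practice

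*Protocol article*

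**What the plan says.** The abstract (Methods/Design) sets three moments: "All tests will be performed at the start of the FTE programme, half way through, and at the end of the programme". The Phase 3 section on the effects of the adjusted FTE repeats this: "The PSQ questionnaire and the tests will be repeated halfway and at the end of the FTE programme". Four measures are followed: the PSQ, the Timed Up and Go test, the 10 metre walking test and a patient-specific performance test.

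For the effect, the Phase 3 Analysis section names one method and no other: "ANOVA for repeated measures will be used to determine the effect of the FTE programme". It does not define an analysis set or mention imputation or a mixed model. The Phase 3 Objective places the effect of the implementation in daily practice and does not limit it to people who finish.

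The planned size follows from three statements: "Fifteen physiotherapists and/or remedial therapists will be recruited" (Phase 2, Participants); each therapist who completes the training "will deliver the FTE programme to two groups of elderly people"; and "Each group consists of six to twelve elderly people aged 70 years or older who have slight problems with activities of daily living" (both Phase 3, Participants).

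**The concern.** Classical repeated-measures ANOVA splits variation within people across a full grid of person by moment. A person with an empty cell does not fit the grid. Unless the value is imputed, that person leaves the analysis of that outcome, together with the values already collected. Deletion works outcome by outcome, so the four measures could end up describing different sets of people.

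Two things are at stake. The first is precision: someone tested at the start and the end but not halfway still carries direct information on the change over the programme, and the method discards it. The second is meaning. People who start FTE and stop are part of what happens when it is introduced in ordinary practices. An estimate from those with all three tests answers a narrower question than the objective asks, and it differs from the all-starters effect whenever stopping is related to change.

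**Working it through.** The article states no sample size calculation, dropout rate or standard deviation for the effect analysis, so there is no figure of its own to reproduce. All rates below are assumptions.

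**1. Implied enrolment.** 15 therapists × 2 groups × 6 to 12 people = 180 to 360.

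**2. Does one gap matter?** A standard routine (statsmodels AnovaRM) was given 30 simulated people at three moments with one value removed. It stopped and reported the data as unbalanced. The person must be removed or the value imputed.

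**3. Share with all three tests.** Let *m* be the chance of missing each repeat test, independent between the two tests, with the start test complete. The share with all three is (1−m)². The share with start and end is 1−m. The difference, m(1−m), is the share with both a start and an end value who are lost only because the halfway value is missing.

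| m (assumed) | all three, (1−m)² | people of 180 to 360 | lost despite start and end, m(1−m) | people of 180 to 360 |
|---|---|---|---|---|
| 5% | 90% | 162 to 325 | 4.75% | 9 to 17 |
| 10% | 81% | 146 to 292 | 9% | 16 to 32 |
| 15% | 72% | 130 to 260 | 12.75% | 23 to 46 |
| 20% | 64% | 115 to 230 | 16% | 29 to 58 |

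With stopping alone at an assumed 10%, 20% or 30%, the numbers left are 162 to 324, 144 to 288 or 126 to 252.

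**4. What the bias depends on.** Let *d* be the share who stop and *r* their mean change divided by that of completers. The all-starters effect is the completer effect × [1 − d(1−r)], so the completer estimate is off by 1/[1 − d(1−r)] − 1.

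| d (assumed) | r = 0 | r = 0.5 | r = 1 |
|---|---|---|---|
| 10% | +11% | +5% | 0 |
| 20% | +25% | +11% | 0 |
| 30% | +43% | +18% | 0 |

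If r exceeds 1, the sign turns: d = 20% and r = 1.25 give 1/1.05 − 1 = −5%. The article contains nothing that fixes r or d.

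**5. A second illustration.** One million people were simulated with a true mean change of 0.30, and stopping before the end test was made more likely after a small halfway gain. The completers' mean change was 0.352 (+17%), 0.396 (+32%) and 0.438 (+46%) at 10%, 20% and 30% stopping. Predicting the missing end values from the start and halfway tests, as an analysis valid under missing at random does in effect, returned 0.30 each time. This works because stopping depended only on observed values.

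**6. Limit of the mixed model.** If people leave before the halfway test, only their start value is known. The model then gives them the change seen in similar people who stayed. If in truth they gained nothing and the start value does not predict stopping, the mixed model lands close to the completer estimate. It does not remove the differences under r = 0 in step 4, so a separate sensitivity analysis is needed.

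**The case against.** The strongest reply is that deletion is inferred. The Analysis section is a short passage in a condensed article, and a full protocol or analysis plan that is not shown could add imputation or fit the repeated measures as a mixed model. This stands as a limit on certainty. It does not remove the point, which concerns the method that the article names and not the lack of a missing-data section.

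A reader might also infer that the plan expects missed tests and throws them away, because "the therapists will keep records of the number of participants who are present and the reasons for any absence". That record belongs to the process evaluation and concerns attendance at sessions. Someone absent from a session may still have all three tests, so it is not evidence of missing outcomes.

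A reader might further infer that the result will be biased towards benefit. No section says how many will stop, why, or how they fare. The nearest figure, from the earlier randomised trial, is that "an average of 90% of the participants attended all the training sessions". It concerns sessions in another study and gives no missing-test rate here, but it does not suggest heavy loss. The 11%, 25% and 43% in step 4 come wholly from assuming that those who stop gain nothing.

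Finally, the Phase 3 Product section speaks of training effects, which could be read as effects in those trained. That reading is possible, but neither that section nor the Objective restricts the effect to people who finish.

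**Conclusion.** The point holds as a default consequence of the method named: with three moments and classical repeated-measures ANOVA, one missing test removes the person from that outcome, precision falls, and the estimate describes completers. At an assumed 5 to 20% missing per repeat test, 90 to 64% of participants remain (162 to 325 down to 115 to 230 of an implied 180 to 360). This rests on independent misses, a complete start test and full enrolment by 15 therapists.

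Bias is conditional: completers overstate the effect if those who stop gain less, agree with all starters if they gain the same, and understate it if they gain more. The documents do not settle which applies. It would go too far to say that the plan prescribes deletion or that its result is known to favour FTE. The change is still worth making, because it costs little and brings the analysis closer to the stated aim.

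**What to change.** In the Phase 3 Analysis section, replace the ANOVA with a likelihood-based linear mixed model for repeated measures, with test moment as a categorical factor. Include everyone with a start test, use all available measurements and delete nobody for an incomplete row.

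Because this is valid only under missing at random, add one sensitivity analysis that sets the change of those who stopped to zero. It is a reference case and not a lower bound, since some may decline. For each outcome, report the number tested at each moment beside the result.

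Calling back people who have stopped for an end test should not be part of this change. The Study design section justifies the absence of informed consent partly by the use of routine data, and such a recall may go beyond that basis.

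The cost is a few lines of text and slightly more analysis work on measurements already planned. The estimate may turn out less favourable.

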#### Product

The effects of the adjusted FTE programme and the adjustments will be documented and made available as products. After the completion of the final phase of the study, the adjustments needed to adapt the FTE programme in daily practices will be known, as will the training effects of the adapted FTE programme. It will also become clear which determinants have affected the outcome of the study. Finally, the study will provide input for a national implementation strategy based on the experiences of this smaller implementation study.

## Discussion

The overall aim of this implementation study is to facilitate the nationwide implementation of a Functional Training Exercise (FTE) programme. Maintaining well-being and independent living, and preventing functional decline in elderly people living at home, are important values in Dutch society. FTE is the first exercise programme for the elderly that achieves sustainable improvements in performance and in the prevention of functional decline. As in many countries, the number of elderly people will increase over the next 25 years in the Netherlands and so the project outcomes will be of interest to policy-makers, insurance companies and health-care professionals, as well as implementation researchers and implementation consultants/advisors.

In our opinion the biggest difficulty with the study will be the recruitment of both therapists and elderly participants. Concerns about therapists include the recruitment of therapists with a continued interest in the FTE programme. Ideally, therapists will be actively involved in the training and homework, implement the FTE in their practice, provide FTE to at least two groups of participants and continue to provide the programme after the end of the study. Furthermore, time and money constraints are a potential threat to actual participation in the study. Another problem is recruiting participants within the time window of the study. Our control of both issues is limited.
